	***Prompts*:**
	-Can you share your feelings about this intervention?
	-What impact do you think this intervention will have on your life?
**Q2**	**What do you think of the content of this intervention?**
	***Prompts*:**
	-Which is your favourite part of this intervention? Why?
	-Which part do you dislike? Why?
**Q3**	**What do you think of the frequency, duration and delivery mode of this intervention?**
	***Prompts*:**
	-What duration of the intervention do you think is suitable for you? Why?
	-What frequency of the intervention do you think is suitable for you? Why?
	-What do you think of the delivery mode of this intervention?
**Q4**	**How about your motivation to exercise?**
	***Prompts*:**
	Has it increased? How and why?
	Are you feeling confident about doing physical exercise?
**Q5**	**What recommendations do you have for this intervention?**

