**Methods and analysis:**

A two-arm pilot randomised controlled trial will be conducted to assess the feasibility, acceptability and preliminary effects of an MBPE program among community-dwelling older people with sarcopenia. A total of 60 participants will be randomised into the intervention group, receiving the MBPE intervention twice a week over 12 weeks, or the control group, receiving health education with the same duration, number of sessions and frequency as the intervention group. Each session of the MBPE program will last about 60 min, including 5-10- min introduction, 20-min MBI, 30-min PE and 5-10-min sharing and discussion. The primary outcomes will be the feasibility (i.e., the time spent recruiting participants, the eligibility rate and the recruitment rate) and acceptability (i.e., the attendance rate, completion rate and attrition rate) of the MBPE program. The secondary outcomes will be the preliminary effects of the MBPE program on symptoms of sarcopenia, motivation for PE, psychological well-being, mindfulness level, physical activity level and quality of life. Individual interviews will be conducted to identify the strengths, limitations and therapeutic components of the intervention. The quantitative data will be analysed by generalised estimating equations. The qualitative data will be analysed by Braun and Clarke’s thematic approach.

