### Objectives and hypothesis

The objectives of this pilot RCT are as follows: (1) to assess the feasibility and acceptability of the MBPE program among community-dwelling older people with sarcopenia; and (2) to investigate the preliminary effects of the MBPE program on the symptoms of sarcopenia, motivation for PE, psychological well-being, mindfulness level, physical activity level and quality of life among this population.

We hypothesise that the MBPE program is acceptable and feasible with the potential to improve the motivation, adherence to PE, physical and psychological health of the older adults with sarcopenia.

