#### 2. Acceptability of the MBPE program

Acceptability will be evaluated using the prospective acceptability, the concurrent acceptability and the retrospective acceptability [56]. Prospective acceptability will be measured as the recruitment rate and the reasons for which older adults did not get involved in the program[56]. Concurrent acceptability will be assessed using the attendance rate (sessions attended by the participants / all sessions), completion rate (sessions in which participants were actually involved and at least 80% completed / all attended sessions), attrition rate (number of participants dropping out / total number of participants) and the reasons for discontinuing [56]. Attrition will be considered if the completion rate is less than 80%. To have a depth exploration of the participants’ experience and avoid leaking privacy, individual interviews will be used to measure the retrospective acceptability, the detailed guideline in Table 3. The individual interviews will be conducted by two researchers who both have experience in individual interviewing and are familiar with sarcopenia and mindfulness. Purposive sampling will be used, and the sample size will depend on the data duration. Reflective journals written by the interviewers will be used to avoid bias and ensure the transparency of the research process [57]. With the participants’ consent, the individual interviews will be carried out face-to-face and audio recorded.

**Table 3 pone.0302235.t003:** Guide to individual interviewing of participants in intervention group.

Number	Questions
**Q1**	**Generally, what do you think of this intervention?**

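### Table 3, question 4: the only prompt on change in motivation names just the hypothesised direction, which may bias the motivation theme of the interviews

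*Protocol article*

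**What the plan says.** Under Acceptability of the MBPE program, the article states that "individual interviews will be used to measure the retrospective acceptability, the detailed guideline in Table 3". Retrospective acceptability is one of three parts of acceptability, and acceptability is one of the two primary outcomes. By its title, Table 3 is for intervention-group participants. The abstract gives the purpose: "Individual interviews will be conducted to identify the strengths, limitations and therapeutic components of the intervention".

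Table 3 has five lead questions, each with prompts. Question 4 leads with "How about your motivation to exercise" and has two prompts: "Has it increased? How and why" and "Are you feeling confident about doing physical exercise".

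Objectives and hypothesis states the expected direction: the programme is thought to be acceptable and feasible "with the potential to improve the motivation, adherence to PE, physical and psychological health of the older adults with sarcopenia". The Conceptual framework section makes motivation the route by which the mindfulness component is meant to increase the benefit of exercise.

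**The concern.** A prompt is used when the open question has drawn a short or vague reply, and that is when its wording has most influence. Here the only prompt on change offers one direction, the one the investigators hope for. A participant whose motivation stayed the same or fell has to contradict the premise to say so.

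Three features of the design add to this. Allocation and blinding says that participants cannot be blinded. The interviews are confined to the intervention group, so there are no control-group accounts to set beside reported increases. And Patient and public involvement, with Strength and limitation, says that participants' views will be used to revise the programme before a full trial. For that purpose, someone whose motivation did not rise is among the most informative interviewees, and the guide does not explicitly invite that answer.

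**Working it through.** No formula applies, and the plan states no figure that depends on this wording. The check is a reading of the whole of Table 3 against the hypothesis, the stated purpose of the interviews and the other measures of motivation.

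**1. Direction of each question's prompts (paraphrased)**

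| Question | Topic | Prompts | Room for an unfavourable answer |
|---|---|---|---|
| 1 | Overall view | 2: feelings; impact on life | Open, no direction named |
| 2 | Content | 2: liked part; disliked part | Explicitly balanced |
| 3 | Frequency, duration, delivery | 3: suitable duration; suitable frequency; view of delivery mode | Open, no direction named |
| 4 | Motivation | 2: increase, with how and why; confidence | Neither prompt names an unfavourable or null answer |
| 5 | Recommendations | 2: what to add; what to change or remove | Invites criticism |

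That makes 2 + 2 + 3 + 2 + 2 = 11 prompts under 5 lead questions. Question 4 is the only one of the 5 whose prompts are all favourably framed. Of its 2 prompts, 1 concerns change in motivation, so the one-directional change wording is 1 prompt of 11.

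**2. Match with the hypothesis.** The hypothesis refers to the programme's "potential to improve the motivation, adherence to PE". The direction named in the change prompt is the same, and no other question in the guide is devoted to motivation.

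**3. Match with the stated purpose.** The abstract wants limitations as well as strengths. Questions 2 and 5 carry this through in their prompts; question 4 does not.

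**4. How far the effect can reach**

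- *Other interview themes.* Questions 1, 2, 3 and 5 are open or invite criticism, so the prompt under question 4 does not shape what they collect.
- *Motivation as a measured outcome.* Secondary outcome measures assigns this to the C-BREQ-2, a self-report questionnaire with five domains including amotivation, taken at baseline and after the intervention. It does not depend on the interview.
- *Feasibility and concurrent acceptability.* Recruitment time and the eligibility, recruitment, attendance, completion and attrition rates are counts or ratios and are unaffected.
- *Sample size and error rates.* Neither uses interview data.

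What remains exposed is the participants' own account of whether, how and why their motivation changed.

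**5. Size.** The article gives no number of interviews and no indication of how often the prompt would be used, so no magnitude can be derived.

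**The case against.** The strongest reply is that the participant first hears an open, neutral question. The prompt is subordinate to it, can be answered with a no, and its second half then asks for the reason. This stands in part: it is why question 4 as a whole cannot be called one-directional. It does not remove the point, because the change prompt still names a single outcome and will be used mainly when the open question has not produced a full answer.

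A second reply points to safeguards: interviewers with interviewing experience, reflective journals, two researchers coding with a third joining the discussion, and recognised rigour criteria. These are real and bear on how answers are interpreted. They do not change a scripted question or recover an answer that was never invited. A skilled interviewer might probe neutrally anyway, but the printed guide does not say so.

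Third, the guide is printed in English for a study in Suzhou, and the wording put to participants is not shown. That is fair. The point applies to the guide as published, and the version used in the field should be checked too.

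A reader might also infer more: that the prompt steers the whole of the retrospective acceptability data, or undermines the trial's evidence on motivation. The article does not support either reading. Four of the five questions are open or invite criticism, and motivation is measured separately by questionnaire. Nor does the article document that participants would give courteous answers; that is a reasonable worry about unblinded interviews, not an established fact.

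**Conclusion.** The point holds in a limited form. The only change prompt under question 4 names the hypothesised direction alone, and the confidence prompt beside it is also favourably framed, in a guide that is otherwise open or balanced. This may bias the motivation theme of the intervention-group interviews. Nothing else in the trial is affected.

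The conclusion rests on two assumptions: that the prompts are used roughly as printed, and that a leading prompt can influence an unblinded participant's answer. The first cannot be verified from the article; the second is ordinary interviewing caution. Severity is low, and the point is worth making because the remedy is free and the interviews will inform the revised programme.

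**What to change.** Reword the two prompts under question 4 of Table 3:

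- Change prompt: *Has it changed – more, less or about the same? How and why?*
- Confidence prompt: *How confident or not do you feel about doing physical exercise?*

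Make the same change in the Chinese version of the guide. The cost is two lines of text. Design, sample, outcome measures and analysis stay as they are. If interviews have already been held with the printed wording, the report should say so and note the direction of the prompt when presenting the motivation theme.

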	***Prompts*:**
	-What do you think should be added? Why?
	-What do you think should be revised or deleted? Why?

### Secondary outcome measures

#### 1. The symptoms of sarcopenia

Following the AWGS 2019 [43], the symptoms of sarcopenia include low muscle mass, low handgrip strength and low 5-time chair-stand test scores. Handgrip strength is the primary efficacy outcome as it is the first-line indicator to diagnose sarcopenia [43]. Muscle mass will be assessed via calculating SMI, appendicular skeletal muscle mass, fat-free body weight and total skeletal muscle mass by bioelectrical impedance analysis (Inbody 270, Korea) [58]. Handgrip strength will be measured by a Jamar dynamometer (Jamar, 563213, USA) as recommended by the American Society of Hand Therapists [59]. The maximum value of dominant hand grip strength will be utilised as the result. In the 5-time chair-stand test, the participants will be invited to stand and sit from a chair (approximately 43 cm high) five times and the time taken to complete this exercise will be recorded. Two tests will be conducted with a 1-min interval and the mean of the test results will be taken.

#### 2. Motivation to exercise

The motivation to exercise will be evaluated using the Chinese version of the Behavioural Regulation in Exercise Questionnaire-2 (C-BREQ-2), which has been tested in Chinese people and shown good consistency (Cronbach’s *α*: 0.72–0.83) [60]. The C-BREQ-2 is a self-report measure with 18 items, divided into five domains: amotivation, external regulation, introjected regulation, identified regulation and intrinsic regulation.

#### 3. Depressive symptoms

Depressive symptoms will be measured with the Chinese version of the short-form Geriatric Depression Scale (GDS-15). The GDS-15 has shown acceptable reliability and validity (Cronbach’s *α*: 0.793, test–re-test reliability: 0.728) in Chinese older adults [61]. Depressive symptoms are classified based on the score as follows: 0–4: normal; 5–8: mild depression; 9–11: moderate depression; 12–15: severe depression [62].

#### 4. Psychological well-being

Psychological well-being will be measured with the Chinese version of Raff’s Psychological Well-being Scale, as adapted by Tan [63]. The Cronbach’s α of this version is 0.89 and the test–re-test reliability is 0.90.

#### 5. Physical activity level

Physical activity level will be evaluated using the Chinese Version of the Physical Activity Scale for the Elderly (PASE-C) [64]. The PASE-C has shown good reliability (intraclass correlation coefficient: 0.81) [65] and validity (fair to moderate association with energy expenditure, walking steps and handgrip strength) [66].

#### 6. Mindfulness level

The mindfulness level of the participants will be assessed using the short Chinese version of the Five Facet Mindfulness Questionnaire (FFMQ-15-C). The FFMQ-15-C is a self-rated scale developed by Zhu et al. [67] with acceptable reliability (Cronbach’s *α* of all five facets: ≥ 0.73). It includes 15 items rated on a 5-point Likert scale, ranging from 1 = ‘never or very rarely true’ to 5 = ‘very often or always true’ to evaluate the five facets of mindfulness: observing, describing, acting with awareness, non-judging and non-reacting.

#### 7. Quality of life

Quality of life will be measured with a questionnaire targeted at sarcopenic older people, namely Sarcopenia and Quality of Life (SarQoL^®^), which was first developed by Beaudart in 2015 and has been translated into more than 30 languages [68]. The Chinese version of SarQoL^®^ was introduced and validated by Li with excellent consistency (Cronbach’s *α*: 0.867) and test–re-test reliability (0.997) [69].

In addition to socio-demographic information, the outcomes will be evaluated at baseline and immediately after the intervention. The assessors will learn and practice the questionnaires or outcome measurements until the re-test reliability is more than 90% before assessment.

### Data management

To protect the security and confidentiality of the data, the personal information (e.g., name, address, contacts) of the participants will be stored on an encrypted hard disk and only the researchers will have access to it. The paper questionnaires will be locked in the researchers’ office. All information collected will only be used for this study and will not be disclosed. A codebook containing information on each variable will be created before the data entry step. All the data will be coded and entered by two researchers independently. Only the core members ([name], [name] and [name]) of this research team can access the data.

### Data monitoring

Throughout the study, the corresponding author ([name]) will monitor recruitment, intervention and retention with the research team ([name], [name] and [name]). The research team will meet regularly to plan and evaluate the daily activities of this study. The procedure of recruitment, the intervention content, the preparation of assessment, training of research assistants, data management and data analysis will be prepared and monitored by the research team. Besides, the intervention fidelity will be checked by two research assistants.

### Statistical analysis

#### 1. Quantitative data analysis

IBM SPSS 23.0 will be used to statistically analyse the data. For continuous variables, the Shapiro–Wilk test will used to evaluate normality. Mean and standard deviation (SD) will used to describe normally distributed data, especially the outcomes to provide information for calculation of standards effect sizes of the subsequent RCT; otherwise, median, interquartile range (P_25_, P_75_) and range (minimum, maximum) will be used.

For continuous variables, an independent-samples *t* test will be used if the data are normally distributed; otherwise, the Mann–Whitney *U* test will be used. Chi-square or Fisher’s tests will be used for categorical data. Feasibility and acceptability will be presented in terms of rate or absolute number based on the nature of the data. The generalised estimating equation model will be used to analyse the preliminary effects of this study. The standardised mean difference with corresponding 95% confidence intervals will be presented to describe the mean differences of both primary and secondary outcomes between the intervention group and the control group [70]. All data analyses will be conducted with two-tailed tests with a significance level of p < 0.05. Both per-protocol (PP) and intention-to-treat analysis will be conducted. The attention rate >80% will be included in the PP analysis.

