### Sample size

25 per group will provide sufficient information for planning the proposed subsequent main randomised trial with an anticipated standardised effect size of about 0.2 on the primary outcome, handgrip strength [46]. Considering a 20% attrition rate [47], the sample size of this pilot RCT has been calculated as 25 × (1 + 20%) = 30 in each group.

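### Mean and SD are reported only for outcomes that pass a normality test, although their stated purpose is to plan the main trial and an SMD is promised for every outcome

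*Protocol article*

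**What the plan says.** All the reporting rules are in the protocol article, Statistical analysis, Quantitative data analysis.

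- Gate: "the Shapiro–Wilk test will used to evaluate normality". No level is given for this test, and the section does not say whether it is applied by arm, by visit or to the pooled sample. A general statement later in the section sets 0.05, two-sided, for all analyses.
- If the data pass: "Mean and standard deviation (SD) will used to describe normally distributed data, especially the outcomes to provide information for calculation of standards effect sizes". The effect sizes meant are those for the later full trial.
- If they fail: "otherwise, median, interquartile range (P_25_, P_75_) and range (minimum, maximum) will be used". No SD is named.
- Effect measure, with no normality condition: "The standardised mean difference with corresponding 95% confidence intervals will be presented to describe the mean differences of both primary and secondary outcomes", comparing the two groups.

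The Sample size section gives the reason for the pilot's size: "25 per group will provide sufficient information for planning the proposed subsequent main randomised trial". For that later trial it expects an effect of roughly 0.2 SD in handgrip strength, which Secondary outcome measures names as the primary efficacy outcome.

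**The concern.** The planning purpose of the mean and SD, and the condition that can remove them from the report, stand in the same sentence. A main trial needs the SD whatever the shape of the distribution, because a comparison of means is sized on the SD. Median, quartiles and range do not supply it except by approximation under a further assumption about shape.

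The rule also sits badly with the unconditional SMD. An SMD is a mean difference divided by an SD. If the table shows only medians and quartiles, the reader has a ratio without its numerator or denominator. The SMD cannot be checked, turned back into kilograms, seconds or scale points, or re-standardised to a different SD.

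At stake is the usefulness of the pilot for its declared purpose. The outcomes most likely to lose their SD are the bounded and skewed scores, for which a planner most needs to see both kinds of summary.

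**Working it through.** **1. The plan's own figure.** 25 × (1 + 0.20) = 30 per arm, as stated in Sample size. The base of 25 rests on a cited rule and cannot be derived from power inputs in the article. The precision figures below use 25 completers per arm.

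**2. What is lost when the test rejects.** SMD = (mean₁ − mean₀) / SD, so raw difference = SMD × SD. The substituted summaries contain none of the mean₁, mean₀ or SD terms.

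**3. How often the test would reject.** The article gives no distributions, so shapes must be assumed. Rejection rates at 0.05 by simulation:

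| Assumed shape | n = 25 | n = 30 | n = 60 |
|---|---|---|---|
| Normal | 5% | 5% | 5% |
| Lognormal, sigma 0.3 | 31% | 37% | 66% |
| Lognormal, sigma 0.5 | 62% | 73% | 97% |
| 0–15 score, rounded normal, mean 4, SD 3 | 25% | 35% | 85% |
| 0–15 score, beta-binomial, mean about 4 | 50% | 61% | 98% |
| 0–15 score, negative binomial, mean 5, size 20 | 27% | 31% | 68% |
| 0–15 score, negative binomial, mean 3.5, size 20 | 38% | 47% | 94% |
| 0–15 score, negative binomial, mean 3.5, size 5 | 53% | 64% | 98% |
| 0–15 score, negative binomial, mean 3.5, size 2 | 81% | 90% | about 100% |

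Negative binomial scores are capped at 15. The 0–15 rows stand for the GDS-15, whose range and bands (0–4 normal) are given in the article. At n = 30 those rows run from 31% to 90%, and more strongly skewed shapes with the same range exceed 90%. If all 60 participants are tested together, rejection is more frequent still, because the test gains power with n. A larger sample therefore makes it more likely that the SD is withheld.

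Even with truly normal data the gate removes some SDs by chance. For 14 independent tests, 1 − 0.95¹⁴ = 0.51 is the probability that at least one rejects.

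**4. How good the SD would be as a planning input.** With 25 per arm the pooled SD has 48 degrees of freedom. Its 95% CI, as a multiple of the estimate and under normality, is √(48/χ²₀.₉₇₅) to √(48/χ²₀.₀₂₅) = √(48/69.02) to √(48/30.75) = 0.83 to 1.25. The required n for a fixed raw difference scales with SD², so this is a factor of 0.83² = 0.69 to 1.25² = 1.56. That is wide, but a planner can work with it.

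**5. How good the SMD would be.** With the article's anticipated effect of 0.2 and 25 per arm:

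- SE = √(2/25 + 0.2²/(4 × 25)) = √(0.0800 + 0.0004) = 0.284.
- An observed SMD of 0.2 has 95% CI 0.2 ± 1.96 × 0.284 = −0.36 to 0.76.
- P(estimate ≤ 0) = Φ(−0.2/0.284) = 0.24. By symmetry P(estimate ≥ 0.4) = 0.24.

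For scale, at 80% power and two-sided 0.05, a target of 0.2 needs 394 per arm and a target of 0.4 needs 100 per arm. With 100 per arm, power at a true 0.2 is 29%. These figures show what would follow if the observed SMD were used as the target. They do not describe a decision in the plan.

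**The case against.** Four points can be made for the plan.

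- **An SD must be calculated.** The SMD is unconditional, so an SD will exist for each continuous outcome, and a fuller document may tabulate it. This stands in part: a reader might infer that the SDs will be missing altogether, and that is too strong. But the article states a reporting rule, and that rule replaces the SD when the test rejects. The problem is a stated rule that conflicts with the next paragraph, not a detail left out.

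- **The planning outcome may be untouched.** Handgrip strength is the outcome named for sizing, and nothing in the article suggests that it would fail the test. This stands. The rejection rates above concern assumed bounded or skewed scores, and their wide range reflects the assumptions.

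- **The plan does not say that the main trial will be sized on the pilot's observed difference.** A reader might infer this from the phrase about effect sizes. But that wording fits equally well with supplying an SD to standardise a separately chosen difference, and Sample size already anticipates about 0.2. The stronger reading is not supported, so the 24%, 394 against 100, and 29% figures mark a risk to guard against.

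- **Significance testing.** The section also states "All data analyses will be conducted with two-tailed tests with a significance level of p < 0.05", and a reader might add that p-values from so small a trial will be taken as proof of effect. The documents do not bear this out as an error. Effects are called preliminary, feasibility and acceptability are the primary outcomes, confidence intervals are planned, and Strength and limitation acknowledges low power. Dropping the tests would be a preference.

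**Conclusion.** The point holds as an internal inconsistency with a practical cost. The rule makes the SD conditional on a normality test, contrary to its stated purpose and out of step with the unconditional SMD in the same section. For bounded or skewed outcomes the SD would often go unreported: from about 30% to over 90% of the time at n = 30 for a GDS-15-like score, depending on the assumed shape and taking 0.05 as the test level. For handgrip strength the probability cannot be known from the article. What is lost is a quantity that 25 per arm estimates to within 0.83 to 1.25 times, while the quantity kept, the SMD, has an SE larger than the effect anticipated (0.284 against 0.2).

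The choice of target difference for the main trial is a matter for a safeguard only, since the plan makes no commitment on it. The change should be made before analysis, but nothing here affects the pilot's feasibility and acceptability outcomes.

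**What to change.** 1. Replace the conditional rule: report mean and SD by arm and visit for every continuous outcome, whatever the Shapiro–Wilk result, and add median, IQR and range where the distribution is skewed. Each SMD can then be reproduced and converted to raw units.
2. As a safeguard, add one sentence saying that the pilot supplies the SD, the baseline-to-post correlation and the attrition rate, and that the main trial's target difference will be set in advance (the anticipated 0.2 or an important difference) and not taken from the pilot SMD.

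The cost is a few more table columns and two sentences of wording. No data collection, sample size or analysis model changes.

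### GEE on two assessments with no stated baseline adjustment, beside a normality switch of unstated scope: a modest, avoidable loss of precision, and means and SDs that may go unreported

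*Protocol article*

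**What the plan says.** All of the analysis wording is in the protocol article, Statistical analysis, 1. Quantitative data analysis.

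- **Method for effects:** "The generalised estimating equation model will be used to analyse the preliminary effects of this study". Model terms, covariates, working correlation and type of standard error are not given.
- **Assessments:** the end of the Secondary outcome measures section says that "the outcomes will be evaluated at baseline and immediately after the intervention", so there are two time points.
- **Normality rule:** "For continuous variables, the Shapiro–Wilk test will used to evaluate normality". Normally distributed data get mean and SD, with the outcomes singled out because they feed the effect-size calculation for the next trial. Other data get median, interquartile range and range.
- **Two-sample tests:** an independent-samples t test "will be used if the data are normally distributed; otherwise, the Mann–Whitney" U test. Chi-square or Fisher's tests serve categorical data. The variables and time point are not named.
- **Reported effect:** a standardised mean difference with 95% confidence interval, promised without any condition on normality.
- **Testing level:** "All data analyses will be conducted with two-tailed tests with a significance level of p < 0.05".
- **Sample size section:** an "anticipated standardised effect size of about 0.2 on the primary outcome, handgrip strength" for the main trial, and "25 × (1 + 20%) = 30 in each group".

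**The concern.** There are two separate issues.

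**Precision.** With one baseline and one post value, the interaction term of an ordinary group-by-time GEE is the difference between arms in mean change. In a randomised trial, adjusting the post value for baseline estimates the same effect with smaller variance. Baseline is already collected for every outcome, so the gain is free. In a pilot of this size, the width of the interval around handgrip strength is most of what the efficacy results can offer.

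**The normality switch.** It is stated for continuous variables in general and is not limited to baseline characteristics. Read literally, an outcome could be tested by GEE and also by a second test that the data choose. More concretely, an outcome that fails Shapiro–Wilk would be summarised by median and quartiles and compared by ranks. Neither gives the mean difference and SD that a standardised mean difference needs, nor the SD needed to size the main trial. For handgrip strength a failure is plausible: both sexes are pooled, and the eligibility table itself uses cut-offs of 28 kg for men and 18 kg for women.

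**Working it through.** **Inputs from the protocol:** two assessments; 25 per group before inflation; 20% attrition; 30 randomised per group; standardised effect 0.2 (anticipated for the main trial); two-sided 0.05.

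**Assumptions:** the baseline-to-follow-up correlation ρ is not in the document, so a range is shown. The outcome variance σ² is taken as equal at both times and in both arms.

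**Step 1, the plan's own figure.** 25 × 1.20 = 30 per group, 60 in total; this reproduces. If 20% are lost, 30 × 0.8 = 24 per group remain, so 24 to 30 per group is the relevant range. The table uses 25.

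**Step 2, variance of the treatment effect, in units of 2σ²/n.**
- Post value only: 1
- Change score (group-by-time GEE): 2(1 − ρ)
- Post value adjusted for baseline (ANCOVA): 1 − ρ²

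The variance ratio of change score to ANCOVA is 2(1 − ρ)/[(1 − ρ)(1 + ρ)] = 2/(1 + ρ). The SE ratio is its square root. For post-only against ANCOVA the SE ratio is 1/√(1 − ρ²).

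**Step 3, numbers.** Power is for a standardised effect of 0.2 at 25 per group, two-sided 0.05.

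| ρ (assumed) | Variance ratio, change/ANCOVA | SE ratio, change/ANCOVA | SE ratio, post-only/ANCOVA | Power, change | Power, ANCOVA |
|---|---|---|---|---|---|
| 0.5 | 1.333 | 1.155 | 1.155 | 10.5% | 12.6% |
| 0.7 | 1.176 | 1.085 | 1.400 | 14.8% | 16.6% |
| 0.8 | 1.111 | 1.054 | 1.667 | 20.0% | 21.7% |
| 0.9 | 1.053 | 1.026 | 2.294 | 35.2% | 36.8% |

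In participants: to match ANCOVA on 25 per group, a change-score analysis needs 25 × 1.333 ≈ 33 per group at ρ = 0.5, or 25 × 1.111 ≈ 28 at ρ = 0.8.

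**Step 4, can a GEE avoid the loss?** Yes, if the two arms are given a common baseline mean. In 1,500 simulated trials with 30 per group, complete data and ρ = 0.5, the empirical SD of the estimated effect was 0.255 for the unconstrained group-by-time GEE, 0.218 for the constrained GEE and 0.218 for ANCOVA. The loss therefore comes from the model terms, not from GEE as such.

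**Step 5, the normality switch against the reporting promise.** One sentence gives means and SDs only to variables judged normal and says that they are needed for the next trial's effect sizes. A later sentence promises standardised mean differences for all outcomes. For an outcome that fails Shapiro–Wilk, the first rule withholds what the second requires. The two fit together only if means and SDs are reported regardless.

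**The case against.** The case on the other side is substantial, and four stronger readings that a reader might infer are not supported.

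- **That the plan decides against baseline adjustment.** It does not say so. An article commonly leaves model terms to fuller documents, and a two-time GEE already uses baseline as a response. As Step 4 shows, one version of it loses nothing. What stands is conditional: the usual, unconstrained model is less precise.
- **That its standard errors will be too small.** This needs an uncorrected sandwich variance with a normal reference, which the document does not specify. Even then the effect is small. With complete data the SE is understated by √((n − 1)/n), about 2%, and type I error is 6.1% at 25 and 5.9% at 30 per group against a nominal 5%. With 20% loss, simulation gave 6.1% to 7.5% (Monte Carlo error about ±1.2 points).
- **That efficacy will be tested by a raw post-value t test.** The t/Mann–Whitney sentence is paired with chi-square and Fisher's tests and may be meant for baseline comparability. GEE is the only method expressly assigned to the preliminary effects. The post-only column above therefore shows what would follow under one reading, not what is planned. The ambiguity itself stands, because nothing limits the rule to baseline data and the same section applies the normality rule to outcome summaries.
- **That attrition will bias the GEE.** No size can be attached to this. The protocol also counts low session completion as attrition, so 20% attrition need not mean 20% missing outcomes. In simulations with loss depending on baseline, bias was at most about 0.01 SD and about the same as for ANCOVA.

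It is also fair that the primary outcomes are feasibility and acceptability, reported as rates or numbers, and that the limitations section concedes low power. That limits the stakes but does not remove the conflict over means and SDs.

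**Conclusion.** The point holds in a limited form. If the GEE is the usual group-by-time model, its standard error is about 5% to 15% larger than that of a baseline-adjusted analysis for ρ of 0.8 to 0.5, and about 3% larger at 0.9. These correlations are assumed. Power for an effect of 0.2 moves by only about two percentage points, so no conclusion of the pilot turns on it. If post values alone were compared, the loss would be larger for ρ above 0.5, but the text does not clearly prescribe that.

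The firmer defect lies in the stated wording. The normality switch has no stated scope, and it can replace the means and SDs that the same section needs for its standardised mean differences and for planning the main trial. This is worth correcting because it costs almost nothing. It does not threaten the primary results.

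**What to change.** Revise the quantitative analysis section before any outcome comparison is made:

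1. For each continuous outcome, name one model for the treatment effect: post-intervention value on arm, baseline value and sex, with t-based inference. A GEE or mixed model with baseline means constrained equal and a small-sample correction is an acceptable alternative. It also keeps participants who have a baseline but no post value, whom ANCOVA alone would drop.
2. Report mean and SD by arm and time for every continuous outcome, whatever Shapiro–Wilk shows. Medians and quartiles can be added.
3. Limit the t and Mann–Whitney tests to descriptive use or a labelled sensitivity check, and say so. Do not let a normality test choose the treatment comparison.
4. Derive the standardised mean difference from the model in item 1 and state which SD is the divisor.

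The cost is a little analysis rewording. No extra data or participants are needed, and the analysis can be run in the planned software.
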